#### Trial Monitoring Processes

This protocol operates as a single-center, investigator-initiated doctoral research study. There are no external third parties nor independent clinical trial monitoring agencies involved in operational auditing. Instead, trial conduct, data entry, and study progress are monitored internally through a structured, dual-tiered academic tracking framework. First, the PhD scholar reports directly to the supervising research guide every month to review day-to-day trial operations, evaluate recruitment milestones, and cross-check master CRF data entries against raw laboratory sheets. Second, formal biannual Doctoral Committee meetings are held every 6 months to comprehensively monitor and audit overall trial progress, verify 100% of signed informed consent records, and ensure strict compliance with protocol safety guidelines and ethical frameworks. The verified monitoring updates are systematically maintained and filed with the IEC during routine reporting windows to guarantee data integrity.

#### Risk-Benefit Balance, Compensation, and Adverse Event Management

Since *sodhana* procedures require temporary modification of diet and lifestyle, to avoid any medical concerns, the participants are kept as inpatients under the supervision of the investigators and trained medical staff throughout the study. As a direct benefit of participation, all diagnostic screenings, including hematology, renal, hepatic, and thyroid panels, will be conducted entirely free of cost. In the highly unlikely event that any adverse event occurs during the trial period, it will be immediately and comprehensively managed medically by the institute at no expense to the participant.

#### Ancillary and Posttrial Care Provisions

Although this trial evaluates safe, standardized clinical protocols with healthy volunteers, full ancillary care is guaranteed throughout the inpatient stay. If a participant develops any routine, non-trial-related acute condition while hospitalized, complete medical management, prescriptions, and consultations are provided onsite entirely free of cost through the institute’s standard clinical infrastructure.

*Saṃsarjana Krama* is structurally embedded as part of the active study intervention. Posttrial care begins immediately following the final postintervention blood draw. Upon protocol completion and official discharge, a direct telephonic support gateway is established for the subsequent 30 days. This gives participants free access to the investigator team and institutional outpatient physicians for any health-related guidance, safety reporting, or routine medical consultations to ensure a smooth transition back to their standard daily routines.

#### Confidentiality and Data Privacy Security

To safeguard participant privacy and comply with biomedical ethics regulations, a strict confidentiality protocol is enforced throughout all phases of the study. Before the trial, personal information collected during the initial registration and screening phase is kept confidential within the hospital’s secure registration logs. During the trial, all enrolled participants are immediately assigned a unique alphanumeric identification code. All subsequent records, CRFs, and laboratory blood collection tubes are labeled exclusively with this code; no names, hospital file numbers, or identifying demographics are attached to biological samples or data entry sheets. Physical documents including signed informed consent forms and raw laboratory data sheets are stored in a locked filing cabinet accessible solely by the principal investigator. Digital datasets are maintained on a password-protected, encrypted local storage drive with no external network connectivity. After the trial, the fully anonymized data will be kept securely for a mandatory archival period of 5 years before permanent deletion, and no identifying personal details will ever be shared with external parties or disclosed in peer-reviewed publications.

### Statistical Measures

The change in values of the outcome measures including MDA, SOD, telomerase activity, and telomere length will be recorded. The data will be tested for normality using the Shapiro-Wilk test. They will be tested for significance using paired *t* tests (if the data are normally distributed) or the Wilcoxon Signed Rank test (if the data are not normally distributed). A *P* value <.05 will be considered significant. All statistical analysis will be conducted using SPSS version 31 (IBM Corp). Moreover, a secondary exploratory subgroup analysis will be conducted within and between the 2 cohorts (*Vamana* and *Virechana* groups) based on the distribution of the data. If the data are normally distributed, within-group analysis will be conducted using paired *t* tests and between-group analysis will be conducted with *t* tests, whereas Wilcoxon Sign Ranked tests and Mann-Whitney *U* tests will be used, respectively, for data that are not normally distributed.

Cohen *d* effect sizes will also be calculated to address the exploratory nature of the study and evaluate the clinical and biological relevance of changes in biomarkers (ie, MDA, SOD, and telomerase activity). Results will be interpreted based on the magnitude and directionality of these effect sizes (small: 0.2; medium: 0.5; large: 0.8) to provide a standardized measure of treatment impact beyond simple *P* value testing.

Given the exploratory, hypothesis-generating design of this pilot study, secondary multivariable analyses will be introduced to evaluate the influence of potential baseline confounders. For normally distributed continuous data, an analysis of covariance (ANCOVA) will compare postintervention outcomes between the 2 seasonal subcohorts (*Vamana* vs *Virechana*) using individual pre-intervention scores as the baseline covariate to mathematically adjust for initial biological variation. Additionally, to evaluate the entire cohort of 53 participants as a unified group, multiple linear regression models will be constructed using the postintervention scores as the dependent variable, entering baseline biomarker values, age, sex, and baseline BMI as independent predictors to systematically control for demographic and physical confounding variables.

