#### Population-Level Summary Measure

The mean intra-individual change score (mean delta difference) will be calculated from baseline to postintervention across the pooled cohort of 53 participants.

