### Core Outcome Set and Summary Measures

Currently, no standardized core outcome set has been developed or registered for the evaluation of Panchakarma procedures (such as *Snehapana, Vamana*, and *Virechana*) in healthy volunteer populations. Consequently, the biomarkers chosen for this exploratory study—MDA, SOD, and telomerase activity—were selected independently based on cellular aging and oxidative stress hypotheses.

The continuous marker of lipid peroxidation (serum MDA levels), biological indicator of antioxidant defense (serum SOD enzyme activity values), and physiological marker of cellular longevity (telomerase activity) will be reported using the mean change from baseline to postintervention (along with the SD and 95% CIs) calculated for the study group. In addition to these mean changes, the proportion of participants experiencing any incidental rescue events (such as the percentage of volunteers) will be tracked descriptively as feasibility and safety outcomes.

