### Sample Size

The sample size is feasibility-driven. It was chosen based on pragmatic constraints. As this is an exploratory study, the goal is not to achieve definitive statistical power but to establish a foundation for future, larger-scale confirmatory research. Analyzing the census of Kerala, only 30% of the population could be sampled as healthy volunteers excluding NCDs, infectious diseases, other systemic illness like cancer, and age. The sample size was calculated as 53 using the following formula;

$$n=\frac{Z_{1-\alpha /2}^{2}\times P(1-P)}{d^{2}}$$

where Z_1-α/2_=1.96 (assuming a 95% CI), *P*=.5 (expected effeciency/anticipated proportion), and d=0.15 (15% margin of error), assuming a dropout rate of 20%.

Although this sample size is rooted in regional screening feasibility, a retrospective sensitivity power analysis confirmed that a finalized cohort of 53 individuals provides 80% statistical power (*α*=.05) to detect a small-to-medium intra-individual effect size (Cohen *d*=0.395) using a 2-sided paired samples framework. This standard biostatistical validation confirmed that, although the enrollment target is grounded in regional fieldwork constraints, it remains mathematically sensitive enough to capture subtle, homeostatic optimization trends in continuous aging biomarkers (MDA, SOD, and telomerase activity) within a healthy cohort.

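### A normality pre-test can switch the primary P value to a Wilcoxon test, which for asymmetric change scores does not test the mean change that the estimand names

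*Protocol article*

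**What the plan says.** The estimand fixes the quantity of interest under Population-Level Summary Measure: "The mean intra-individual change score (mean delta difference) will be calculated from baseline to postintervention across the pooled cohort of 53 participants". Core Outcome Set and Summary Measures follows it: each marker "will be reported using the mean change from baseline to postintervention", with SD and 95% CI, and without reference to the test used.

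Statistical Measures chooses the test from the trial's own data. First, "The data will be tested for normality using the Shapiro-Wilk test". Then: "They will be tested for significance using paired *t* tests (if the data are normally distributed) or the Wilcoxon Signed Rank test" if they are not normal. The level of the normality test is not given. It is not clear whether it is applied to the raw values or to the changes; the sentence just before it speaks of the change in values. The same rule is repeated for the comparisons within and between the two seasonal cohorts.

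Significance is judged by "A *P* value <.05 will be considered significant". Primary Outcome asks in addition for a moderate to large Cohen d. Sensitivity Analyses uses P<.05 alone: if significance agrees between the available-case analysis and the baseline-carried-forward analysis, the findings count as stable.

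The secondary between-season model carries its own normality condition: "For normally distributed continuous data, an analysis of covariance (ANCOVA) will compare postintervention outcomes". No alternative is stated for non-normal data. The multiple regressions carry no such condition.

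Sample Size states 80% power at Cohen d=0.395 with 53 participants, "using a 2-sided paired samples framework".

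**The concern.** The paired t test addresses a zero mean change. The Wilcoxon signed-rank test addresses symmetry of the changes around zero (a zero pseudo-median). The two agree when the changes are symmetric and part company when they are not. A non-normal result therefore alters both the method and the hypothesis, while the reported mean, its CI and Cohen d stay with the mean.

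Three things are at stake. The P value and the CI for one marker may point in different directions. The chance of P<.05 when the mean change is zero may exceed 5%. And the power figure, derived for a paired comparison of means, may not describe the test that is actually run.

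**Working it through.** **The plan's own power figure.** Inputs from Sample Size: n=53, d=0.395, two-sided alpha .05. Noncentrality = 0.395 × √53 = 0.395 × 7.280 = 2.876 on 52 degrees of freedom. Power by the noncentral t distribution is 0.806. The stated 80% is reproduced, for a paired t test.

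**Why the two tests differ.** The protocol gives no SD, skewness or distribution for the changes, so a shape must be assumed. Take change = lognormal(0, s) minus its mean, so that the true mean change is exactly zero. Its skewness is (exp(s²)+2) × √(exp(s²)−1):
- s=0.3: 3.094 × 0.307 = 0.95
- s=0.5: 3.284 × 0.533 = 1.75
- s=0.7: 3.632 × 0.795 = 2.89

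At s=0.5 the median change is 1 − exp(0.125) = −0.133. A change falls below zero with probability Φ(s/2) = Φ(0.25) = 0.60. The mean is zero, yet about 60% of participants change in one direction, and Wilcoxon responds to that.

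**P<.05 when the mean change is zero, n=53.** Shapiro-Wilk is applied at .05 to the changes (an assumption), then the selected test at two-sided .05. The last two columns are from 2,500 simulated trials per setting and the Shapiro-Wilk column from 4,000.

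| Skewness | Shapiro-Wilk rejects | Two-stage rule | Fixed paired t |
|---|---|---|---|
| 0.95 | 60% | 7.5% | 4.6% |
| 1.75 | 94% | 16% | 5.9% |
| 2.9 | 99.7% | 27% | 6.4% |

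A run of 20,000 trials per setting gave 16.4% against 5.8% at s=0.5. With gamma-distributed changes it gave 6.1% at skewness 0.5 and 9.7% at skewness 1, and with exponential changes (skewness 2) 23.3%. At s=0.5 with fewer pairs the two-stage rate is 14.1% (43 pairs) and 11.0% (27 pairs, the number in the spring cohort so far).

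**Where there is no inflation.** The same 20,000-trial run at n=53 gave these two-stage rates:
- normal changes: 5.3%
- symmetric heavy-tailed changes (t with 3 df): 5.0%
- lognormal biomarkers with the same distribution before and after (correlation 0.5): 5.1% at log-SD 0.5 and 5.0% at log-SD 1, although Shapiro-Wilk rejects in 48% and 96% of samples

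If the means are equal but the spread shrinks, the changes become skewed. Log-SD going from 0.5 to 0.4 gives 6.3%, from 0.5 to 0.3 gives 10.0%, and from 0.8 to 0.4 gives 28.1%.

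**Power at d=0.395, n=53, skewness 1.75.** With the long tail in the direction of the effect, the two-stage rule has 64% power and the fixed t test 88%. With the long tail in the opposite direction, the figures are 93% and 77%.

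**The joint criterion.** Reading moderate to large as d of at least 0.5 requires |t| ≥ 0.5 × √53 = 3.64, a condition on the mean. In 8,000 mean-zero trials per setting, P<.05 with d≥0.5 occurred in 0.19%, 0.26% and 0.62% at s=0.3, 0.5 and 0.7. The percentages were the same whichever rule supplied the P value.

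**The case against.** The strongest reply is that Primary Outcome does not rest on P alone. With Cohen d required to be at least 0.5, the mean-based condition dominates and the choice of test hardly matters. This stands. A reader might infer that the trial's success criterion has several times its nominal error; the calculations do not support that. What remains exposed are the statements that use P alone, in Statistical Measures and Sensitivity Analyses.

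A reader might also infer that skewed biomarkers are enough to cause the problem. They are not. The skew has to be in the changes. If the procedure leaves the distribution unchanged, the changes are symmetric and both tests hold their level. Nor is pre-testing itself the cause, since it adds almost nothing under normality. The excess arises because the Wilcoxon branch tests another quantity. When it rejects with a zero mean, it may be detecting a real shift in most participants, only not the shift that the estimand names.

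A third inference, that normality is checked on raw values and not on the changes, cannot be drawn either, because the wording is ambiguous.

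Finally, the trial is exploratory, the mean change with CI is reported in any case, and results are also to be read by effect size. This lowers the practical weight but does not remove the mismatch between the P value and the estimand.

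**Conclusion.** The point holds in a limited form. The protocol fixes a mean-change estimand and then allows the primary P value to come from a test that, for asymmetric changes, does not address that mean. This is visible in the text and needs no simulation.

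Its size rests on an assumed shape. Under mean-zero shifted-lognormal changes at n=53, the P-only rate is about 7.5%, 16% and 27% at skewness of about 0.95, 1.75 and 2.9, against about 5% to 6% for a fixed paired t test. Inflation of threefold or more (16/5 = 3.2) thus needs skewness of about 1.75 or higher, and nothing in the protocol shows that the changes will be that skewed. With symmetric changes the rate is near 5%. Under the same assumed skewness of 1.75, power at d=0.395 could be well below or above the stated 80%, depending on the direction of the tail.

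The correction is worth making because it is cheap and the Results section says that data analysis is still pending. It does not overturn the joint criterion under Primary Outcome.

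**What to change.** Before the pending data are analysed, name one primary analysis of the mean change for every marker, whatever a normality test shows: the paired t test with its 95% CI, or a bootstrap CI for the mean change. Keep the Wilcoxon signed-rank test as a sensitivity analysis, and say that it addresses a different quantity.

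If a marker is to be analysed on the log scale, say so in advance and restate its estimand as a ratio of geometric means. Otherwise the log scale itself departs from the mean-change estimand.

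Run the secondary between-season ANCOVA without the normality condition, with residual checks and robust standard errors.

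The cost is wording in Statistical Measures and the matching sentence in the abstract. The statistical downside is that under severe skew the raw-scale t test is slightly above its nominal level, about 6% to 7% in the more skewed settings tabulated. In an extreme case (lognormal changes with log-SD 1) it reached 9.9%, against 51.6% for the two-stage rule.

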#### Primary Variables (Endpoints)

The endpoints consist of continuous laboratory biomarker change scores measuring oxidative stress indicators, specifically MDA and SOD, and cellular longevity parameters, including telomerase activity.

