### Limitations

Placebos for procedures like *Vamana* and *Virechana* are challenging to include; therefore, this study does not include a control group. However, the resulting single-group study design raises concerns about internal validity.

In addition, this exploratory pilot trial lacks a concurrent, untreated parallel control group. Since this study operates as an investigator-initiated doctoral project embedded within a real-world clinical service, introducing an untreated healthy cohort was operationally and ethically unfeasible, as all recruited individuals are actively seeking immediate wellness interventions. To mitigate this constraint and maximize data validity, each participant serves as their own internal longitudinal control through structured pre- and postintervention paired comparisons. Furthermore, potential lifestyle and environmental confounding variables are strictly controlled by housing all 53 participants within an identical inpatient ward environment throughout the active study timeline.

We acknowledge that serum MDA and T-SOD are short-term surrogate markers of oxidative stress, not direct proof of delayed aging. In this protocol, *Śodhana* represents a complete therapeutic process including *Pūrvakarma* (internal oleation), *Pradhāna Karma* (*Vamana* or *Virechana*), and *Saṃsarjana Krama*. Therefore, acute changes in MDA and T-SOD reflect the immediate metabolic shifts of this entire multiphase cycle rather than long-term aging changes. To address this limitation, we paired these dynamic redox markers with telomerase activity. This allows us to explore whether the intense physiological “reset” caused by the complete *Śodhana* sequence correlates with any stabilizing effects on a deeper, genetic marker of cellular longevity.

The sample size calculation was also pragmatic rather than inferential. The exploratory nature of the study warrants a focus on feasibility of the protocol rather than to test the hypothesis.

The recruitment is seasonal and consecutive. Therefore, differences in environmental factors, including the climate and diet, as well as baseline biological rhythms between the 2 cohorts may act as potential modifiers for biomarker levels.

Although other biomarkers, including an interleukin panel and the microbiome, are available, we included only a limited number of biomarkers for our healthy volunteers due to financial constraints.

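### Baseline adjustment between the seasonal cohorts is made conditional on normal data, so a skewed marker is left with only an unadjusted Mann-Whitney test

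*Protocol article*

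**What the plan says.** All the relevant rules are in the protocol article, Methods, Statistical Measures.

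- **Normality check.** "The data will be tested for normality using the Shapiro-Wilk test". The article does not say whether this means raw values, changes or model residuals. The sentence before it concerns changes: "The change in values of the outcome measures including MDA, SOD, telomerase activity, and telomere length will be recorded".
- **Unadjusted comparison of the cohorts.** It is labelled secondary and exploratory. It uses *t* tests when data are normal; otherwise Wilcoxon (within cohort) and Mann-Whitney (between cohorts) "tests will be used, respectively, for data that are not normally distributed". Whether the Mann-Whitney test uses post values or changes is not stated.
- **Adjusted comparison of the cohorts.** "For normally distributed continuous data, an analysis of covariance (ANCOVA) will compare postintervention outcomes between the 2 seasonal subcohorts", "using individual pre-intervention scores as the baseline covariate". No version is named for data that are not normal.
- **Pooled regression.** "multiple linear regression models will be constructed using the postintervention scores as the dependent variable, entering baseline biomarker values, age, sex, and baseline BMI". No cohort term is listed and no normality condition is attached.

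Elsewhere, the estimand section says "The endpoints consist of continuous laboratory biomarker change scores measuring oxidative stress indicators". Trial Design states that participants join a cohort by self-selection according to season. Limitations allows that climate, diet and "baseline biological rhythms between the 2 cohorts may act as potential modifiers for biomarker levels".

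**The concern.** ANCOVA assumes roughly normal residuals around the fitted line. It makes no such demand on the outcome values or on the changes. Whichever of those two quantities is tested for normality, the check is made on the wrong one.

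The consequence is a rule that drops a covariate the trial already holds, marker by marker. MDA might be compared with baseline adjustment while T-SOD or telomerase is compared without it, so the three contrasts would not estimate the same thing. The pooled regression does not fill the gap, because without a cohort term it cannot compare the cohorts. It also shows that the condition has no stated rationale: it is a linear model of post value on baseline with the same residual assumption, and it is planned without a normality condition.

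Two things are at stake in this secondary comparison. One is precision. The other is the error rate when cohorts that were not randomised differ at baseline.

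**Working it through.** **The plan's own figures.** The article gives no figure for the between-cohort comparison. Its power statement (53 participants, Cohen d 0.395, two-sided 5%, 80%) concerns the paired comparison. It reproduces at 0.806 with the noncentral *t* distribution and is not in dispute.

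**Inputs from the document.** Total 53; 27 in the Vamana cohort so far; significance level 0.05.

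**Assumed inputs, because the document gives none.** 26 in the Virechana cohort (53 − 27); lognormal marker with log SD 0.6; pre-post correlation ρ of 0.5 to 0.7 on the log scale; baseline shift between cohorts of 0 or 0.5 SD; for power, a true difference of 0.6 SD.

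**Step 1: would the condition often switch adjustment off?** If raw values are what is tested, Shapiro-Wilk at n = 53 rejects lognormal data in 61% of samples at log SD 0.3, 93% at 0.5 and 100% at 0.8. The condition buys little in return. With skewed data (log SD 0.5 or 0.8, ρ 0.3 to 0.7) and no baseline shift, ordinary raw-scale ANCOVA kept its error rate at about 4-5%.

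**Step 2: what each method estimates when there is no cohort effect.** Take a baseline shift of δ = 0.5 SD and equal variances on the log scale. The apparent cohort difference is:

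| Method | Shift regresses toward the mean | Shift is a stable level difference |
|---|---|---|
| Post values | ρδ = 0.25 to 0.35 | δ = 0.50 |
| Change | −(1−ρ)δ = −0.25 to −0.15 | 0 |
| ANCOVA | 0 | (1−ρ)δ = 0.25 to 0.15 |

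The standard-error factor is √(1/27 + 1/26) = 0.275. It multiplies an SD of 1 for post values, √(2(1−ρ)) = 1.00 to 0.77 for change, and √(1−ρ²) = 0.87 to 0.71 for ANCOVA. As an example, for post values at ρ = 0.5 with regression to the mean, 0.25/0.275 = 0.91, which gives a normal-theory rejection rate of about 15%.

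**Step 3: simulated rejection rates at a nominal 5%, δ = 0.5 SD, ρ 0.5 to 0.7.** Repeat runs move by one to two percentage points.

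| Method | Regresses toward the mean | Stable level difference |
|---|---|---|
| Mann-Whitney, post values | 13-23% | about 41% |
| Mann-Whitney, change | 11-14% | about 5% |
| ANCOVA, log scale | about 5% | 12-17% |

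**Step 4: simulated power, no baseline shift, true difference 0.6 SD, ρ 0.5 to 0.7.**

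| Method | Power |
|---|---|
| Mann-Whitney, post values | 54-55% |
| Mann-Whitney, change | 55-78% |
| ANCOVA, log scale | 68-85% |

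The normal-theory values for ANCOVA agree: 0.6/(0.87 × 0.275) gives about 71% at ρ = 0.5, and 0.6/(0.71 × 0.275) gives about 86% at ρ = 0.7.

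**The case against.** The strongest reply is that losing the ANCOVA need not distort the comparison. The estimand defines the endpoints as changes, and Statistical Measures opens with changes, so the Mann-Whitney test may well be meant for change scores. A seasonal influence such as climate or diet could raise or lower both measurements of a participant who starts and finishes within one season. Subtraction then removes it. In that case the Mann-Whitney test on change keeps its 5% and the ANCOVA does not. **This stands.** A reader might infer that the unadjusted test necessarily turns baseline differences into apparent effects; the documents do not support that. Nor do they support making ANCOVA the only comparison. In cohorts that were not randomised, change-score and baseline-adjusted analyses answer different questions, and both can be shown.

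Three further points also stand. The article says only that the data are tested, so it is a reader's inference that raw values are meant. Limitations says that differences may matter; it does not predict a baseline imbalance or give its size. And the comparison is secondary and exploratory, with seasonal confounding already disclosed.

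It could also be said that the method for skewed markers belongs in a statistical analysis plan. That reply is weaker. The article does not leave the matter open: it states a condition for the adjusted analysis and ties it to the wrong quantity. Nothing in the objection gives a reason to let a Shapiro-Wilk result decide whether baseline is used.

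**Conclusion.** The point holds in a limited form. The stated condition on the ANCOVA is badly set, and for a marker that fails the normality test it leaves no baseline-adjusted comparison of the cohorts.

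The firmest cost is precision. When there is no baseline shift, power falls from 68-85% to 54-55% (post values) or 55-78% (change). Inflation of the error rate depends on two things the document does not fix or cannot know: which variable enters the Mann-Whitney test, and whether a baseline difference persists. Post values do badly in both scenarios tried; change scores do badly in only one of them.

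All these sizes rest on the assumed skewness, correlation, shift and 27-to-26 split, and should be read as illustrations. The primary pooled pre-post analysis and the success criteria for MDA and SOD are not affected.

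**What to change.** 1. Delete the opening condition of the ANCOVA sentence in Statistical Measures. Fit post value on baseline value and cohort for MDA, T-SOD and telomerase whatever the normality result.
2. Check the residuals. If they are clearly skewed, log-transform both baseline and post values and report the adjusted ratio with its 95% CI.
3. If an unadjusted between-cohort test is kept, state that it is run on change scores rather than post values, and report it beside the ANCOVA.
4. Label the contrast as exploratory and confounded by season, whichever method is used.

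The cost is a few words removed and two or three sentences added. No new data are needed. The small downside is that skewed markers are reported as ratios.

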## Methods

### Trial Design

This open-label, exploratory clinical trial consists of a single group and a primary endpoint of decreasing serum MDA values and increasing serum SOD values within 18 days to 20 days after *Vamana* in *Vasantha ritu* and *Virechana* in *Sarad ritu*. The participants will be recruited by the principal investigator consecutively by season: *Vamana* cohort in the *Vasantha ritu* (spring season) and *Virechana* cohort in the *Sarad ritu* (autumn season). Each participant is enrolled into only one seasonal arm based strictly on their chronological window of voluntary registration. There is no active assignment of participants; instead allocation follows a participant-driven, self-selection framework. The total study duration is 3 years. The study is registered in the Clinical Trial Registry-India (CTRI; CTRI/2024/02/062176).

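### The secondary Vamana-versus-Virechana comparison cannot separate procedure from season or self-selection, and the pooled regression has no cohort term

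*Protocol article*

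**What the plan says.** Under Trial Design, the Vamana cohort is recruited in spring and the Virechana cohort in autumn. Each participant enters one arm only, "based strictly on their chronological window of voluntary registration". The same section says that nobody is actively assigned and that participants select themselves.

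Statistical Measures sets P<.05 as the significance rule and then plans three analyses that involve the cohorts:

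- Unadjusted tests: "a secondary exploratory subgroup analysis will be conducted within and between the 2 cohorts", by t test or Mann-Whitney U between groups.
- An ANCOVA that "will compare postintervention outcomes between the 2 seasonal subcohorts", "using individual pre-intervention scores as the baseline covariate to mathematically adjust for initial biological variation". The baseline score is the only covariate named.
- A multiple linear regression "to evaluate the entire cohort of 53 participants as a unified group", "entering baseline biomarker values, age, sex, and baseline BMI as independent predictors to systematically control for demographic and physical confounding variables". No cohort, season or procedure term is listed.

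Limitations acknowledges that recruitment is seasonal and consecutive, and that climate, diet and biological rhythms "may act as potential modifiers for biomarker levels". It does not mention self-selection. It also says that housing everyone in the same ward strictly controls lifestyle and environmental confounding.

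The Population-Level Summary Measure of the estimand is the pooled mean change from baseline in 53 participants, not a contrast between cohorts.

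**The concern.** A between-cohort test of Vamana against Virechana invites a reading about the procedures. Here every Vamana participant is a spring participant and every Virechana participant an autumn one, and each cohort consists of whoever chose to register in that season. The season caveat in Limitations changes nothing in the planned tests, and a shared ward cannot make spring and autumn alike.

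The regression raises a related problem. It pools two procedures given in two seasons and is presented as adjusting for confounders, yet the variable that marks both differences is not in the model.

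At stake is the use of the secondary results. The protocol describes the study as hypothesis-generating and plans a multi-arm randomised trial next. An apparent ranking of the two procedures could feed that design although these data cannot support one.

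**Working it through.** **Inputs.** From the protocol: target 53; 27 Vamana participants as of April 4, 2025 (Results); paired d=0.395 with 80% power (Sample Size). Assumed: 26 in the Virechana cohort (53 - 27 = 26, if no further Vamana participants are added), and all seasonal shifts, baseline gaps and baseline-to-post correlations below. The documents give none of these.

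**1. The protocol's own power figure.** A two-sided paired t test with n=53, d=0.395 and alpha .05 has power 80.6%, against 80% stated, so the figure reproduces. It covers the pooled paired test only; the protocol claims no power for the between-cohort contrast. With 27 versus 26, an unadjusted two-sample t test needs d=0.78 for 80% power and has 29% power at d=0.395.

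**2. Can procedure and season be separated?** Code procedure as 0 for Vamana and 1 for Virechana, and season as 0 for spring and 1 for autumn. The columns are identical, so the design matrix [1, procedure, season] has rank 2 for 3 columns. Added covariates cannot make the two effects separately estimable.

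**3. Seasonal change during the treatment window.** The planned ANCOVA was simulated with zero procedure difference, r=0.5, 27 versus 26, and 3,000 trials per row:

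| Assumed season shift (SD) | Mean ANCOVA difference (SD) | Trials with P<.05 |
|---|---|---|
| 0 | 0.00 | 4% |
| 0.25 | 0.25 | 18% |
| 0.5 | 0.50 | 54% |
| 0.8 | 0.80 | 91% |

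The whole shift appears as a Vamana-Virechana difference, because the baseline covariate carries no information about it.

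**4. A stable baseline difference.** The ANCOVA contrast is (difference in post means) - r x (difference in baseline means), where r is the within-cohort slope, equal to the correlation when variances are equal. If each cohort would stay at its own mean and nothing changes, both differences equal the same gap, so the contrast is gap - r x gap = (1 - r) x gap. For an assumed gap of 0.5 SD:

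- r=0.6: (1 - 0.6) x 0.5 = 0.20 SD
- r=0.3: (1 - 0.3) x 0.5 = 0.35 SD

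Simulation with 27 versus 26 returns the same values, with P<.05 in roughly 13-14% and 24-25% of trials respectively, against a nominal 5%.

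**5. Leaving cohort out of the pooled regression.** In a simplified model (baseline, age, optional cohort term; r=0.5) the true age coefficient is zero and the cohorts differ in age by an assumed 0.5 SD:

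| Assumed cohort shift (SD) | Age coefficient without / with cohort | Residual SD without / with cohort |
|---|---|---|
| 0 | 0.00 / 0.00 | 0.86 / 0.86 |
| 0.5 | 0.06 / 0.00 | 0.89 / 0.86 |
| 1 | 0.13 / 0.01 | 0.99 / 0.87 |

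The omission does no harm if the cohorts do not differ. Otherwise it moves the coefficients of covariates that differ between cohorts and inflates the residual SD.

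**The case against.** The strongest reply is that these analyses are labelled secondary and exploratory, that the protocol itself calls the groups seasonal, and that Limitations names climate, diet and biological rhythms. Nowhere does the protocol say the contrast will show one procedure to be better. All participants must also be eligible for both procedures and pass the same screening, which narrows differences between the cohorts. All of this stands and keeps the point modest. It does not remove it: an exploratory label excuses low power, but not a contrast that cannot be estimated, and common eligibility does not equalise who registers in which season.

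A reader might infer several stronger things that the documents do not support:

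- *That calendar time and assay batch are also the same variable as procedure.* Recruitment from March 2025 to December 2026 can span more than one spring and autumn, and the protocol does not say when or in what batches samples are assayed.
- *That ANCOVA is necessarily biased here.* The (1 - r) x gap result needs cohorts with stable, different means. If a baseline gap is chance variation around a common mean, ANCOVA is unbiased and the change-score comparison is the one that misleads. The documents do not settle which holds, and the 0.5 SD gap is an illustration only.
- *That the power figures contradict the plan.* They do not, since no power is claimed for this contrast. The value 0.78 is for the unadjusted test; at r=0.6, ANCOVA's detectable difference is about 0.78 x sqrt(1 - 0.36) = 0.63 SD.
- *That the regression claims to control season.* Its claim is limited to demographic and physical confounders.

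**Conclusion.** The concern holds in a limited form. That procedure and season coincide, under self-selection, follows directly from Trial Design and needs no assumption. The planned between-cohort tests and the baseline-adjusted ANCOVA therefore estimate a difference between two procedure-plus-season packages in self-selected groups, not a procedure effect. Limitations goes part of the way but does not carry the point into the analysis or mention self-selection.

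How misleading the contrast could be depends on unknowns. Under the assumed seasonal shifts of 0.25 to 0.8 SD, P<.05 arises in about 18% to 91% of trials with no procedure difference. Under an assumed stable 0.5 SD baseline gap, the artefact is 0.20 to 0.35 SD for r between 0.6 and 0.3. The 27/26 split is an assumption throughout.

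The missing cohort term is a specification fault in a secondary model, affecting its residual variance and covariate coefficients. It would be wrong to infer that the primary result is compromised by either point: the pooled paired pre-post test does not use the between-cohort contrast or the regression.

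**What to change.** In Statistical Measures:

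1. Add cohort (spring Vamana package / autumn Virechana package) as a factor in the pooled regression.
2. Report the between-cohort contrast as an estimate with 95% CI, labelled as a package difference not attributable to procedure, and draw no P<.05 conclusion from it.
3. State that the regression does not control season or self-selection.

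The cost is one degree of freedom in a model of 53 participants, plus wording. Data collection does not change, and the protocol reports that data analysis is still pending. The cohort term improves the pooled model but does not make the procedure effect identifiable, so item 2 is needed as well.
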